## Introduction

### Slow-release oral morphine as an alternative OAT

Methadone and buprenorphine/naloxone are common pharmacological treatments for opioid use disorder (OUD) aimed at reducing unregulated opioid use, overdose risk, and associated harms.[1–10] However, not all individuals respond well to these treatments, necessitating alternative options such as slow-release oral morphine (SROM), extended-release naltrexone, extended-release buprenorphine, and injectable opioid agonist therapies.[6,8,11] Methadone, a full mu-opioid receptor agonist, has long been the gold standard for OAT due to its high retention rates but requires careful dose titration due to its long half-life, overdose risk, and potential for QT (a measure of the heart’s electrical cycle on electrocardiogram) prolongation.[12] Buprenorphine/naloxone, a partial agonist, has a better safety profile but exhibits a ceiling effect on opioid receptor activation, which may limit its efficacy for individuals with high opioid tolerance.[6]

In contrast, SROM is a full agonist with a long-acting formulation which provides stable plasma levels with once-daily dosing without a ceiling on its opioid effects, making it a potential alternative to methadone and buprenorphine/naloxone. Additionally, unlike methadone, SROM does not prolong the QT interval and may have a lower risk of sedation.[13–15] Originally developed for pain management, SROM has gained recognition as an opioid agonist treatment (OAT) in several countries, including Austria, Germany, and Canada, though its regulatory approval status varies. SROM, marketed as Kadian^®^, a 24-hour extended-release morphine capsule, was introduced in 2017 under British Columbia, Canada’s (BC) provincial drug plan (PharmaCare) as an off-label option for individuals who have not found success with methadone or buprenorphine/naloxone, though it is unclear who are most likely to benefit.[5,6]

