### Adapting clinical guidelines to a new drug landscape

Clinical guidelines in BC had previously regarded SROM as a third-line treatment behind buprenorphine/naloxone and methadone but updated their guidance in 2023, in response to rising overdose death rates across the province, to remove the tiers and advise collaborative treatment selection based on client preferences, clinical judgement and contextual circumstances.[6] Guidance for SROM is largely based on clinical consensus and expert opinion due to overall limited evidence to support decision-making.[6] This client-centered shift acknowledges that prior experiences with OAT often shape future treatment decisions. SROM may be an alternative option for individuals who have experienced negative outcomes with other OAT medications, such as incomplete elimination of withdrawal with buprenorphine/naloxone, or intolerable side effects with methadone, including sedation, emotional blunting, or cardiac risks such as QT prolongation.[11] Individuals with contraindications to methadone, including ventricular arrhythmias or concurrent use of QT-prolonging medications, may particularly benefit from SROM as the medication does not affect the QT interval.[11] Moreover, frequent or early switching between OAT options is often a signal of suboptimal treatment fit, whether due to poor tolerability, inadequate therapeutic response, or individual treatment goals not being met.[6,11]

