### Covariate selection

We propose to include all selected confounders identified in a recent methadone versus buprenorphine/naloxone study,[61] which applied a modified disjunctive cause criterion[62] to the augmented list of covariates from systematic reviews.[63,64] These covariates include socio-demographic factors, measures of disease severity and comorbidity, and OAT-related factors. Additionally, COVID-19-related covariates will be included to control potential selection bias introduced by pandemic-related service disruptions and differential treatment accessibility (see Table 4 for the list of covariates).

All time-varying covariates will be updated weekly. These covariates will be used to estimate the inverse probability of treatment as well as censoring weights to adjust for measured confounding and informative censoring respectively.

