where $SW_{it}$ is the stabilized weight for the *i*th individual at time t, $C_{ij}$ is the censoring status for the *i*th individual at *j*th time, ${\bar{C}}_{ij}$ is the censoring history for the *i*th individual at *j*th time, $L_{i0}$ is the list of time-fixed covariates including treatment arm, ${\bar{L}}_{ij}$ is the time-dependent covariate history for the *i*th individual at *j*th time. Time-dependent covariates will be lagged by one week to ensure censoring is predicted using prior-week covariates. Same set of baseline and time-varying covariates will be included in the treatment and censoring models. Both treatment weights at time zero and censoring weights will be stabilized, truncated at the 99th percentile to limit the influence of extreme values and their product will be used as the final weights.[72] Covariate balance will be assessed using standardized mean differences (SMD), with SMD <0.10 considered balanced.[77] To fit the marginal structural model, a pooled weighted logistic regression model will be fitted to compare the time to OAT discontinuation, all-cause mortality, and overdose-related acute care visits across treatment groups. Based on the fitted models, individual time-to-event (survival) probabilities will be predicted weekly for each treatment arm by setting the treatment equal to a specific value (e.g., SROM, methadone, or buprenorphine/naloxone) for all individuals. These predicted probabilities will then be averaged across the population to get week-specific survival probabilities. The risk of the events will be estimated as one minus the averaged survival probability, with risk differences calculated for SROM initiators versus buprenorphine/naloxone and methadone. We will report hazard ratios, risk differences, and risk curves. Compatibility intervals and curves will be computed using the approach described in the Statistical analysis section.

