### hdPS estimation

As a sensitivity analysis, the treatment weights in the initiator analysis will be estimated using hdPS approach, an alternative to propensity score weighting, to address potential residual confounding, particularly for unmeasured differences in the severity of OUD and medical comorbidities among treatment groups. This semi-automated, data-driven method will identify proxy variables from administrative data for inclusion in propensity score models.[75] We will extract covariates from five data sources: DAD diagnostic codes (ICD-10, 4 digits), DAD procedure codes (5 digits), MSP diagnostic codes (ICD-9, 3 digits), MSP fee codes (5 digits), and PharmaNet drug therapeutic class 5 code (8 digits). Proxy variables will be assessed within a six-month window before time zero with exclusions for variables related to investigator-selected covariates, exposure, outcomes, colliders, and known instruments. Proxy covariates appearing in <50 individuals will be excluded to avoid concerns of positivity violations. To refine selection, three recurrence variables will be created for each candidate proxy (any occurrence, frequent occurrence above the median, and frequent occurrence above the 75th percentile), with duplicates removed. A Cox-LASSO regression will rank and select the top 200 covariates per outcome.[78] The selected empirical covariates, combined with investigator-selected covariates, will be incorporated into propensity score models estimated using multinomial logistic regression models or penalized regression methods such as LASSO to estimate the treatment weights.[79] In the marginal structural model, we will apply pooled weighted logistic regression using the final weights—calculated as the product of hdPS weights and censoring weights from the initiator analysis—to estimate hazard ratios, risk differences, and risk curves. Compatibility intervals and curves will be computed using the approach described earlier.

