Severe mental disorder (ever)^‡, a^	Yes/No	Includes major depressive disorder, bipolar disorder, and schizophrenia, and identified through ICD codes if diagnosed ever and updated if diagnosed during episode follow-up.
Alcohol use disorder (ever)^‡, a^	Yes/No	Identified through ICD codes and DIN/PIN, if diagnosed ever and updated if diagnosed during episode follow-up.
Hepatitis C virus (ever) ^‡, a^	Yes/No	Identified through ICD codes if diagnosed ever and updated if diagnosed during episode follow-up.
Asthma (ever)^‡, a^	Yes/No	Identified through ICD codes* and DIN/PIN within the past year, updated during the follow-up.
Chronic pain in past year^‡, a^	Yes/No	Identified through ICD codes within the past year, updated during follow-up.
Chronic obstructive pulmonary disease^‡, a^	Yes/No	Identified through ICD codes within the past year, updated during the follow-up.
Charlson comorbidity index in past year^‡^	0 and above	Using the Charlson comorbidity index[66] and hospitalization records within the past year, and updated during the follow-up.
Dispensations of psychiatric or sedative medication in the past month^‡, a^	Yes/No	Identified through DIN/PIN of dispensations in the past 30. Updated during the follow-up.
*Factors related to OAT experience*		
Dispensations opioid other than OAT in the past month^‡, a^	Yes/No	Identified through DIN/PIN and a case-finding algorithm used prior[67] and updated during the follow-up.
Received prescription opioids other than OAT prior to OUD diagnosis ^a^	Yes/No	Identified through DIN/PIN and a case-finding algorithm used prior[67] and updated during the follow-up.
Treated tobacco use disorder in past year^‡, a^	Yes/No	Based on ICD-10 codes and indication of nicotine replacement therapy in PharmaNet
Attachment to the prescriber ^‡, a^	Yes/No	Identified based on billing history from the physician. More than 50% of physician billing attributed to the prescriber in the past 12 months
Funding of prescribers who initiated OAT: alternative payment plan	Yes/No	Alternative payment plan indicated by the absence of a medical services plan billing record (capturing fee-for-service billing) at initial OAT dispensation.
Urine drug test in the past week^‡^	Yes/No	Receipt of urine drug test from physician billing records
Practice size^‡^	Large, medium, small	Determined by network analysis; number of unique OAT clients in past 12months. Large for >300 clients, medium for 16–300 clients and small for ≤15 clients.
*COVID-19 related factors*		

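### Table 4 has no prior overdose, no graded prior-OAT history and no lagged OAT dose, leaving recorded confounders out of the treatment and per-protocol censoring weights

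*Protocol article*

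**What the plan says.** The Covariate selection section takes its list from an earlier two-drug comparison ("We propose to include all selected confounders identified in a recent methadone versus buprenorphine/naloxone study"), adds COVID-19 items and points the reader on ("see Table 4 for the list of covariates"). The Initiator analysis section then fixes how the list is used: "Same set of baseline and time-varying covariates will be included in the treatment and censoring models". The Per-protocol analysis section estimates its censoring weights by the same approach.

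Table 4 has a block headed "Factors related to OAT experience". Its seven rows are non-OAT opioid dispensing, prescription opioids before OUD diagnosis, treated tobacco use disorder, attachment to the prescriber, prescriber funding, urine drug testing and practice size.

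The Introduction describes SROM as "an off-label option for individuals who have not found success with methadone or buprenorphine/naloxone". It adds: "Clinical guidelines in BC had previously regarded SROM as a third-line treatment behind buprenorphine/naloxone and methadone". The tiers were removed in 2023, and cohort entry closes on 31 December 2022.

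**The concern.** In this cohort SROM was given largely to people for whom another OAT had not worked. How often, how recently and with which drug they had tried OAT should therefore predict who starts SROM, and also who discontinues, overdoses or dies. Prior overdose is a marker of severity of the same kind. If neither enters the propensity model, part of any SROM contrast may reflect who was selected for it.

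The per-protocol analysis has a second gap. For (i)–(viii), people are censored when their dose falls below the benchmark or they switch. For (ix) and (x), clones are censored according to whether and when a switch occurs. Recent dose and missed days are natural predictors of both events. Censoring weights that ignore them may not remove the selection they are there to remove.

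**Working it through.** **1. What Table 4 contains.** It has 25 rows: 7 socio-demographic + 8 comorbidity + 7 OAT experience + 3 COVID-19. None is prior overdose. None is the number, type, dose, length or recency of earlier OAT. None is current or lagged OAT dose, or missed days. Footnote a to the table defers only code lists, not further variables. A Table 5 footnote mentions the number of treatment interruptions before time zero, but it puts no variable into any model.

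**2. Does the protocol treat prior OAT as a confounder?**
- Treatment choice: the two background statements quoted above, plus the remark under Adapting clinical guidelines that earlier OAT experience shapes later treatment decisions.
- Outcome: Table 2 says recent OAT experience may affect current response, and that completing both inductions may signal complex needs or higher tolerance.

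The list rests on a modified disjunctive cause criterion, and the protocol's own text links prior OAT to both exposure and outcome.

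**3. What the sub-population restrictions already control.**

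| Sub-population | Prior OAT | Prior overdose |
|---|---|---|
| (i) | Fully controlled: none since 1996 | Not controlled |
| (ii) | Not controlled beyond the short gap | Not controlled |
| (iii)–(viii) | Yes/no history by drug, time window or completed induction. Number of attempts, finer recency, last dose and prior SROM stay free | Not controlled |
| (ix), (x) | Starting drug fixed, earlier history free | Not controlled |

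**4. Are the variables available?** Study design says PharmaNet supplies dispensing dates and doses. Study population uses OAT look-back to 1996. Key measures codes overdose-related acute care as an outcome. Limits: in-hospital OAT and overdoses not seen by a clinician are not captured, as the protocol says. Study status describes the data obtained as June 2017 to December 2022. The sub-population definitions already need an earlier look-back, so the two statements should be reconciled.

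**5. Back-up analyses.** Table 5 marks hdPS and IV as initiator only. hdPS uses a six-month window on DAD, MSP and PharmaNet codes, without NACRS emergency records, and applies "exclusions for variables related to investigator-selected covariates, exposure, outcomes, colliders, and known instruments". OAT and overdose codes may therefore be screened out.

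**6. Illustrative size.** The documents give no figure to reproduce and no inputs. For one omitted binary factor, the bias factor is

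[1 + p1(RR − 1)] / [1 + p0(RR − 1)]

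Here p1 and p0 are its prevalences in SROM and comparator initiators, and RR is its effect on the outcome. All inputs are assumed.

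| p1 / p0 | RR 1.5 | RR 2 | RR 3 |
|---|---|---|---|
| 0.4 / 0.3 | 1.20/1.15 = 1.04 | 1.4/1.3 = 1.08 | 1.8/1.6 = 1.13 |
| 0.4 / 0.2 | 1.20/1.10 = 1.09 | 1.4/1.2 = 1.17 | 1.8/1.4 = 1.29 |
| 0.6 / 0.3 | 1.30/1.15 = 1.13 | 1.6/1.3 = 1.23 | 2.2/1.6 = 1.38 |

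Where restriction makes the prevalences equal (0 and 0 for any prior OAT in (i); 1 and 1 for the defining history in (iii)–(viii)), the factor is 1.00.

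**The case against.** A reader might infer that the main confounders go uncontrolled throughout. The documents do not support that. Prior OAT is removed by design in (i) and controlled by drug, time window or completed induction in (iii)–(viii). Table 4 also carries correlates of severity, such as housing, incarceration, mental disorder, alcohol use disorder and sedative dispensing. What stays open is the intensity of history within strata, the history in (ii), (ix) and (x), and prior overdose everywhere.

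A reader might also count dose as a confounder of every contrast. Dose after time zero cannot confound the initiator contrast. The point about lagged dose concerns the per-protocol censoring weights only.

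It may also be tempting to call hdPS and IV useless. That goes too far. Screening out exposure- and outcome-related codes does not remove correlated proxies, and the IV analysis is aimed at uncontrolled confounding. The protocol also names residual confounding as a limitation. These are partial back-ups for the initiator analysis and give none for the per-protocol analyses.

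Nor can one say that the source study's own list lacked these variables, because that study is not at hand.

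Finally, the bias factors rest wholly on assumed inputs. They apply a risk-ratio formula to hazard ratios and treat the omitted factor as independent of the adjusted covariates. All of this stands and narrows the point. It does not explain why recorded variables that the protocol itself treats as important are missing from the list.

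**Conclusion.** The concern holds in this limited form. Followed as written, Table 4 leaves three sets of recorded variables out of the weights: prior medically attended overdose in all ten sub-populations; graded OAT history in (ii), (ix) and (x), and within the strata of (iii)–(viii); and lagged dose and missed days in the per-protocol censoring models. Both primary outcomes are affected.

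The size is unknown. The range of about 1.04 to 1.38 shows what one omitted binary factor could do under the assumed values. It is not an estimate from the documents. Its direction, against SROM, also assumes that the factor is commoner among SROM initiators and raises the risk of the outcome. No size was worked out for the censoring-weight gap.

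**What to change.** Add to the baseline covariates in Table 4:
- for all sub-populations, overdose-related acute care in the past year;
- for (ii)–(x), number of prior OAT episodes, type and last dose of the most recent OAT, longest prior episode and time since last OAT, with a no-prior-OAT category wherever first-time users are included.

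Add to the per-protocol censoring models, lagged by one week:
- OAT dose and missed days;
- interim overdose visit, but only where overdose is neither the outcome nor part of it. Where overdose is the outcome, follow-up ends at the first visit and the indicator is constant.

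Report SMDs for the added variables. Inspect the weight distribution and positivity, especially around week 4. There the stated benchmarks rise from ≥30 to ≥80 mg for methadone and from ≥140 to ≥480 mg for SROM, so lagged dose may come close to determining who is censored. If a variable is left out, give the reason.

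The cost is a few variables derived from linked community dispensing and acute-care records, and somewhat more variable weights, more so where SROM is rare in a history stratum. The protocol reports that no analysis has started, so the list can still be changed beforehand.

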### Statistical analysis

We will adjust for all baseline covariates to estimate the initiator effect as hazard ratios, differences of cumulative incidence (risk) at 24 month, and risk curves using a marginal structural Cox proportional hazard regression model (MSM) with inverse probability of treatment weighting.[71,72]. For the per-protocol analysis, additional time varying confounding will be adjusted via censoring weights to mitigate selection bias from artificial censoring due to receipt of dose below key benchmark, treatment switching, violation of eligibility criteria including initiating pregnancy, incarceration, or treatment taper. However in the ‘clone-censor-weight’ approach for the sub-population (ix) and (x), we will not artificially censor for the violation of dosing benchmark and will estimate the artificial censoring weights conditional on their covariate history. Sandwich variance estimates will be used to compute the 95% compatibility (confidence) intervals for the adjusted hazard ratios,[73] while 500 bootstrap samples (with replacement) would be used to compute the compatibility intervals for risk differences and compatibility curves for risk curves.[74] We will apply high-dimensional propensity score (hdPS) and instrumental variable (IV) approaches for the initiator analysis as sensitivity analyses.[75,76] While the MSM and ‘clone-censor-weight’ approaches will target the marginal treatment effect, the IV analysis will estimate a local average treatment effect among compliers, i.e., individuals who would be prescribed the treatment preferred by treating physician or facility (see details in IV estimation section later). We will use SAS version 9.4 to prepare analytic data and conduct the statistical analysis using the SAS and R version 4.5.0.

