### Initiator analysis

We will apply a multinomial logistic model to estimate the probability of initiating SROM, methadone or buprenorphine/naloxone, incorporating selected baseline covariates, to adjust for confounding by indication at time zero. The treatment weights will be estimated by taking the inverse of the probability of initiating the observed form of OAT. The selection bias induced by censoring due to death or loss to follow-up will be controlled via censoring weights estimated from a pooled logistic regression model.^67^ To estimate weekly censoring weights, the model will incorporate an indicator for week (modelled with cubic splines), product of week and medication, and both time-fixed and time-varying covariates ().

$$SW_{it}=\prod_{j=1}^{t}\frac{\mathrm{Pr}.(C_{ij}=0|L_{i0},{\bar{C}}_{i,j-1}=0)}{\mathrm{Pr}.(C_{ij}=0|L_{i0},{\bar{L}}_{ij},{\bar{C}}_{i,j-1}=0)},$$

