Follow-up	Intention-to-treat (ITT): from time zero to outcome, death, loss to follow-up, 24 months after time zero, or December 31, 2022, whichever occurs first. Per-protocol (PP): additionally, we will assess adherence weekly and censor follow-up at protocol violation (see Table 3).	Same.
Causal contrasts	ITT for the sub-populations (i) to (viii) and PP for all.	Treatment initiator analysis for the sub-populations (i) to (viii), and PP for all.
Analysis plan	ITT: Hazard ratios will be estimated using Cox PH model. To obtain risk curves and risk differences at 24 months, we will estimate the baseline hazard and combine it with covariate effects to compute cumulative risks. To adjust for potential selection bias due to loss to follow-up, we will use inverse probability weighting (IPW) as a function of baseline and time-varying covariates. PP analysis: same except that individual are censored at non-adherence and uncensored individuals are assigned IPW that are a function of baseline and time-varying variables.	*For the study population (i) to (viii)* Initiator analysis: Marginal structural models with treatment weights from propensity scores models and censoring weights due to loss to follow-up. Weights will be estimated as a function of baseline and time-varying covariates. PP: Same as initiator analysis except potential pre- and post-baseline confounders that are associated with adherence to the treatment strategies will be included in the censoring models. *For the study population (ix) to (x)* Same PP analysis as applied to the study population (i) to (viii), except that individuals’ clone are used with a modified censoring mechanism (see Table 3).

* The optimal SROM doses are determined applying 1:6 MET-to-SROM conversion rate as per BC guidelines.[6]

**Table 2: T2:** Target study populations for comparative effectiveness analysis

Study population	Definition	Rationale
Incident users	(i) No history of OAT dispensation, dating back to January 1, 1996	To evaluate treatment outcomes among individuals initiating OAT for the first time
Prevalent new users	(ii) No dispensation for ≥5 days of methadone and SROM and ≥6 days for buprenorphine/naloxone	To capture repeated OAT attempts after a washout period, reflecting common real-world patterns.

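### Risk curves and 24-month risk differences are tied to a proportional-hazards model, and no treatment-by-week term is stated for the outcome models that produce them

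*Protocol article*

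**What the plan says.** The Statistical analysis section lists, besides the hazard ratio and under a treatment-weighted model, these initiator results: "differences of cumulative incidence (risk) at 24 month, and risk curves using a marginal structural Cox proportional hazard regression model (MSM". Table 1, in the target-trial column, says "Hazard ratios will be estimated using Cox PH model" and obtains cumulative risks by combining the baseline hazard with covariate effects. Its emulation column says only that marginal structural models will be used.

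The Initiator analysis section describes the fitting: "To fit the marginal structural model, a pooled weighted logistic regression model will be fitted to compare the time to OAT discontinuation", and likewise for the other outcomes. From that fit, "individual time-to-event (survival) probabilities will be predicted weekly for each treatment arm by setting the treatment equal to a specific value", and "The risk of the events will be estimated as one minus the averaged survival probability". No time function and no treatment-by-time product is listed for this outcome model. The hdPS and Per-protocol sections also use pooled logistic outcome models and add no such term. The IV section takes its risk curves from a Cox proportional-hazards model.

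A week-by-medication product appears once, for the censoring weights: "To estimate weekly censoring weights, the model will incorporate an indicator for week (modelled with cubic splines), product of week and medication".

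**The concern.** A model with one constant treatment term yields a single ratio, averaged over the event times. Risk curves predicted from it keep that ratio at every week: they cannot cross, and they cannot separate early and then converge except as a constant ratio allows. If the true ratio changes, early and late effects are blended.

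The article itself gives three reasons to expect change:

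- The dosing benchmarks in Key measures differ between week 1, weeks 2-3 and week 4 onward, so the per-protocol strategies being compared are not the same in each phase.
- For mortality and overdose, the initiator follow-up in Table 3 is not censored at switching or discontinuation, so the initial contrast can be expected to dilute over 24 months.
- In sub-populations (ix) and (x) each person is cloned into both strategies and may be consistent with both up to day 30. The two arms therefore largely share events in that period, and the early ratio is close to 1 by construction. Any later effect makes the hazards non-proportional.

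Risk differences and risk curves are the results a clinician can read directly, and discontinuation is a primary outcome with a plausible early peak.

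**Working it through.** **No figure to reproduce.** The article states no event rate, effect size or sample size. All rates below are assumptions. The 104-week horizon comes from the 24-month follow-up limit.

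**True risk.** For arm a with weekly hazard h_a(t), the risk by week w is R_a(w) = 1 − ∏(1 − h_a(t)) over t = 1 to w.

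**Modelled risk.** Take the large-sample limit of a pooled logistic model, logit p = α_t + βA, with a free intercept for each week, one common treatment term, equal arms and no censoring. With S_a(t) the true proportion still at risk, the α_t and β solve
- S_0(t)(p_0 − h_0) + S_1(t)(p_1 − h_1) = 0 for each week t, and
- Σ S_1(t)(h_1 − p_1) = 0 over all weeks.

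The modelled risks are then 1 − ∏(1 − p_a(t)).

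**Discontinuation, comparator 15% per week for 4 weeks then 3%; HR 0.5 for 4 weeks then 1.**
- Week 4, true: comparator 1 − 0.85^4 = 0.478; treated 1 − 0.925^4 = 0.268; difference -21.0 points.
- Week 104, true: 0.97^100 = 0.0476. Comparator 1 − 0.522 × 0.0476 = 0.975; treated 1 − 0.732 × 0.0476 = 0.965; difference -1.0.
- Modelled: common odds ratio 0.756. Week 4 risks 0.413 and 0.336, difference -7.7; week 104 risks 0.983 and 0.955, difference -2.8.

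**Range of cases, same discontinuation rates** (risk differences in percentage points):

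| HR weeks 1-4, then later | Week 4 true | Week 4 modelled | Week 104 true | Week 104 modelled |
|---|---|---|---|---|
| 0.5, then 1 | -21.0 | -7.7 | -1.0 | -2.8 |
| 0.8, then 1 | -7.8 | -3.3 | -0.4 | -1.0 |
| 0.8, then 0.9 | -7.8 | -5.2 | -1.4 | -1.8 |
| 1, then 0.7 (clone-type) | 0.0 | -6.1 | -3.8 | -2.5 |
| 0.8 throughout (check) | -7.8 | -7.3 | -2.8 | -2.9 |

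The last row shows that the distortion comes from the changing ratio and not from the logistic approximation, which accounts for at most about half a point.

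**A second set of discontinuation rates** (12% in weeks 1-4, 6% in weeks 5-12, 2.5% after) with HR 1.5 for 4 weeks then 0.8: true +14.8 at week 4 and -1.2 at week 104; modelled +3.1 to +3.6 and +1.3 to +1.5. The modelled ranges run from no censoring to administrative censoring under uniform entry. Here the 24-month difference changes sign.

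**Mortality, assumed 0.0006 per week; HR 0.5 for 26 weeks then 1.33.**
- Week 26, true: 1 − 0.9994^26 = 0.0155 against 1 − 0.9997^26 = 0.0078, difference -0.77. Modelled (odds ratio 1.117): 0.0110 against 0.0123, difference +0.13.
- Week 104, true: 0.0605 against 0.0677, difference +0.72. Modelled: 0.0606 against 0.0675, difference +0.69.

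For a rare outcome the early curve takes the wrong sign, while the 24-month difference is nearly preserved.

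**The case against.** The strongest objection is that the defect is partly read from silence. The Statistical analysis section is a summary that names a model family. The operative text is in the Initiator analysis section, where the pooled logistic model is given no terms at all, not even the function of week it must contain to predict weekly survival. Such a model can carry a treatment-by-week product, the authors do use one where they spell out the censoring model, and a fuller plan may specify it. This stands in part. A reader might infer that the plan forces the curves into a fixed ratio; the text does not settle that, and it holds only if the proportional-hazards form is followed. The objection does not remove the point, because the article does more than stay silent: it names proportional hazards as the source of the risk differences and curves, and Table 1's target-trial column and the IV section say the same.

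A second objection is that a reader might infer that both early and 24-month differences would be wrong for every outcome. The calculations do not support that. For rare mortality the 24-month difference, the only time point the article names for risk differences, barely moves.

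Third, no rate or hazard ratio comes from the article, and the larger distortions need a marked change in effect. That is correct; with HR 0.8 then 0.9 the week-104 error is about 0.4 points.

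Fourth, spline-by-treatment terms may be unstable in small SROM strata with few deaths. That is a fair limit on how the change is made.

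**Conclusion.** The point holds in conditional form. The article names a proportional-hazards structure for the risk differences and curves, and states a week-by-medication product only for the censoring model. If the outcome model is fitted as named, changing effects are averaged.

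Under the assumed rates, the discontinuation risk difference at week 4 is understated by 4.5 points (-7.8 against -3.3) to 13.3 points (-21.0 against -7.7) when an early benefit fades to none. In the same two cases the 24-month difference is overstated by 0.6 to 1.8 points, and where the effect reverses it can change sign. For rare mortality the harm is confined mainly to the early part of the curve. With a constant ratio there is essentially no harm. The sizes depend wholly on assumed rates and ratios. The expectation that the ratio changes rests on the article's own design features.

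This should be corrected before analysis. It does not invalidate the design.

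**What to change.** In every pooled logistic outcome model used for risk curves and risk differences (initiator, hdPS, per-protocol and clone-based), state a flexible function of week and its product with medication. Where SROM strata or deaths are too sparse for this, use weighted non-parametric risk curves. Reword the Statistical analysis section so that it agrees with the Initiator analysis section on which model yields the risks, and describe the single hazard ratio as a time-averaged summary. Curves from the Cox-based IV analysis should either allow the effect to vary over time or be labelled as resting on proportional hazards.

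The cost is a few model terms and some rewording. Intervals will be somewhat wider, and estimates may be unstable in small SROM strata. Study status and timeline reports that no analyses have been conducted, so the change can still be made in advance.
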